#### Secondary outcome measures

1) erector spinae muscle size and composition 2) gluteal muscles size and composition 3) lumbar extensor and gluteal muscles strength, 4) pain, 5) disability, 6) health related quality of life, 7) kinesiophobia, 8) catastrophizing, 9) depression/anxiety, 10) level of physical activity and 11) sleep quality.

##### MRI assessment of erector spinae and gluteal muscles morphology

The same method, as described above for the multifidus muscle, will be used to assess the erector spinae morphology and composition at each lumbar level. Similarly, a routine pelvic MRI T2-weighted and IDEAL (Lava-flex, 2 echo sequence) will also be acquired to assess gluteus maximus, gluteus medius and gluteus minimus muscle size and composition. IDEAL axial water and fat images will be used to calculate the percent fat-signal fraction: %FSF = (Signal_fat_/[Signal_water_ + Signal_Fat_] × 100) of each muscle. The Horos DICOM viewer software will be used for imaging analysis.

##### Lumbar extensor muscles strength

Lumbar extensor muscle strength will be evaluated by the MedX lumbar extension machine. Participants’ hips, knees, and pelvis will be secured to the machine to ensure isolation of the lumbar extensor muscles with a fixed axis of movement between the L5-S1 vertebral levels. This dynamometer measures isometric lumbar extension muscular strength (torque) in a seated position and allows dynamic resistance through a full 72° range of motion (ROM). Therefore, the maximum lumbar extension torque will be measured as maximum voluntary isometric contraction (MVIC) in lumbar extensor muscle strength in seven positions: 72°, 60°, 48°, 36°, 24°, 12° and 0° of flexion [53, 54]. Participants will be seated and positioned in the apparatus. A belt will be fastened over the thighs and tightened until they can no longer lift their buttock’s off the seat. A fixation will be positioned a few inches above the participants’ patella, and they will rest their feet on a platform that will also be tightened to restrict any movement of the heels beyond one inch. Participants’ will also have a neck support at the base of their occipital bone. Initial testing will be performed to verify any limitations in their ROM and adjustment for the counterweight [55]. Participants will initially perform a slow controlled warm up for approximately 1 min, and then the maximum strength test will begin [53]. Verbal encouragement will be provided to motivate participants to generate maximum torque. The movement arm of the MedX machine is linked to a load cell that is interfaced with a computer, which will record and calculate torque measurements.

##### Gluteal muscle strength

A hand-held dynamometer (micro FET2; Hoggan Health Industries) will be used to assess gluteal muscle strength. Participants will be placed on a therapy table in a prone position with their arms by their side to assess gluteus maximum muscle strength with the knee at 90 degrees of flexion and the thigh/hip slightly extended (e.g., off the table). Participants will be instructed to maintain this position for 5 s, creating an isometric contraction in the form of a “make” test and asked to exert a maximal force against the hand-held dynamometer. Measurements will be recorded in newton/torque. All participants will have a submaximal practice trial and then 3 measurements will be obtained on each side, with a 30 to 45 s break in between each trial. The mean of the 3 measurements will be used in the analysis. Similarly, patients will be placed in a side lying position with their arms by their side and with their top leg abducted, slightly extended and externally rotated to test the gluteus medius muscle. Again, participants will be instructed to maintain this position for 5 s, while exerting a maximal force against the hand-held dynamometer. Three measurements will be acquired on each side. Two certified ATs will be acquiring the measurements. Hand-held dynamometry has been shown to be a valid [56] and highly reliable tool to assess gluteus muscle strength [57] and has been recommended as a practical standard for clinical setting.

#### Questionnaires

Secondary self-reported outcome measures will include, disability/function status, pain, pain related fear including catastrophizing and kinesiophobia, function, depression, anxiety, level of physical activity and sleep quality obtained from self-reported questionnaires. Participants will be asked to complete the Canadian Minimum Data set, the Short-Form 12 Item Survey questionnaire (SF-12), modified Oswestry Low Back Pain Disability Index (ODI) and numerical pain rating scale will be used to measure patients’ disability/functional status and related pain. The Pain Catastrophizing Scale (PCS) and the Tampa Scale of Kinesiophobia (TSK) will be used to measure pain related fear. The Hospital Anxiety and Depression Scale (HADS) will be used to assess depression and anxiety, and the International Physical activity questionnaire (IPAQ) and Insomnia Severity Index (ISI) will be used to assess the level of physical activity and sleep disturbances, respectively. All questionnaires have previously demonstrated a good level of test–retest reliability and have been validated in patients with chronic LBP [58–67].

##### Disability

The ODI will be used to assess participants’ level of self-reported disability in relation to LBP. It is a 10-item scale in which each item is rated from 0 to 5, where 0 signifies that their pain does not influence that situation and a score of 5 signifies severe disability. Pain, walking, lifting, sitting, standing, personal care, sleeping, travel, sex life, and social life are categories included in the questionnaire. Scores are classified as minimal, moderate, severe, crippled, or bed bound. The ODI has shown good reliability and validity, and therefore is deemed to be the gold standard of measuring disability related to LBP [68].

##### Health related quality of life

The 12-item SF-12 is the condensed form of the past 36-item survey and will be used to measure participants’ health-related quality of life. The 12-item survey consists of eight domains that measure both physical and mental components of health: 1) limitations in physical activities due to health problems, 2) limitations in social activities due to physical or emotional problems, 3) limitations in usual role activities due to physical health problems, 4) bodily pain, 5) general mental health (psychological distress and well-being), 6) limitations in usual role activities due to emotional problems, 7) vitality (energy and fatigue) and 8) general health perceptions. Scores from each of the 12 questions are summed to calculate an overall score between 0 and 100, with a score of 100 representing the highest level of health. Since this is a condensed version of a longer and established questionnaire, it has been widely tested and considered to be both reliable and valid [69, 70].

##### Pain

The Numerical Pain Rating scale (NPR) will be used to measure participants’ level of pain. This tool is a self-reported rating system for pain intensity. The NPR has excellent reliability and validity, and can be used to identify statistical and clinically significant changes in perceived pain [61, 71].

##### Catastrophizing

The PCS is a 13-item questionnaire that will be used to measure participants’ level of catastrophizing. Each item is rated from 0 to 4 for a possible total of 52. The questionnaire focuses on three domains that have been used to portray catastrophizing: attentional focus on pain related thoughts (rumination), exaggeration of painful stimuli (magnification), and adopting a hopeless orientation with coping (helplessness). A higher score indicates a higher level of catastrophizing, with scores above 30 being clinically significant. This measure is both reliable and valid [62, 72].

##### Kinesiophobia

The TSK will be used to assess participants’ fear of movement or reinjury in the presence of pain. The TSK- 11 includes 11 phrases related to kinesiophobia, such as “I’m afraid I might injure myself if I exercise”, with each phrase rated with a Likert scale from 1 to 4. Scores range between 11 to 44 with higher scores indicating increased levels of kinesiophobia. This measure has been found to have high reliability and validity [63].

##### Depression

The HADS is a 14-item questionnaire that will be used to measure participants’ level of depression and anxiety. Seven items are associated with depression and 7 are associated with anxiety. Cognitive, behavioural, and emotional symptoms are involved in the questionnaire. Each item is rated from 0 to 3 with either depression or anxiety having scores between 0 and 21, with 21 as the highest possible level. Scores between 0 to 7, 8 to 10, and 11 to 21 are categorized as normal, borderline, and abnormal/elevated for any domain, respectively. This tool was deemed to be both reliable and valid [64].

##### Sleep

The ISI will be used to measure self-reported quality of sleep. It includes 7 questions that assess the ability to fall asleep, the ability to stay asleep, and sleep effects on daily life. Each question is rated with a Likert-scale from 0 to 4, with lower ratings representing a higher quality of sleep. Scores between: 0 and 7 indicate no clinically significant insomnia, 8 to 14 indicate subthreshold insomnia, 15 to 21 indicate moderate insomnia, and 22 to 28 indicate severe insomnia. Fourteen is commonly used as the cut-off score to detect primary insomnia. This tool has been found to be both reliable and valid [67].

##### Physical activity: international physical activity questionnaire (IPAQ)

The IPAQ will be used to measure participants’ level of physical activity. The IPAQ is a self-reported log of physical activity (METs based on intensity) in minutes per week over a period of 7 days. The level of physical activity is ranked either vigorous (8 MET), moderate (4 MET), walking (3.3 MET) and sitting/rest (1 MET) and must be allocated to the right category. The number of minutes per category is then combined, and the results are then organized as high, moderate, or low physical activity based on the total MET minutes. The reliability and validity of this measure has been demonstrated [66].

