### Procedure

Eligible participants will be randomized into an aquatic therapy group or land-based standard care group. The intervention period will last 10 weeks, with a frequency of 2 times a week for each group at the School of Health, Concordia University. This frequency of training is in accordance with previous related exercise intervention studies for chronic LBP [19]. The duration of 10 weeks was chosen as strength improvements from training largely occur within that time period [51]. All methods will be carried out in accordance with relevant institutional guidelines and regulations. Written consent form will be obtained from all participants prior any data collection, and will be obtained to publish this paper.

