### Data collection

All outcomes will be obtained at baseline for both intervention groups. All baseline assessments (e.g. MRI, strength, questionnaires) will be repeated at the end of the intervention during a 10-week follow-up (refer to Table S1 in Appendix). All self-reported questionnaires will be completed in-person using paper forms. Imaging outcomes (e.g., MRI) and lumbar extensor muscle assessments (e.g., strength) will be acquired at the School of Health, Concordia University. Demographic characteristics will be acquired via a self-reported questionnaire at baseline, after randomization.

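### As written, the IPAQ scoring rule adds sitting minutes to the MET-minute total that grades physical activity

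*Protocol article*

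**What the plan says.** The rule is in the protocol article, section *Physical activity: international physical activity questionnaire (IPAQ)*. Activity is recorded "in minutes per week over a period of 7 days" and is "ranked either vigorous (8 MET), moderate (4 MET), walking (3.3 MET) and sitting/rest (1 MET) and must be allocated to the right category". The text goes straight from the sitting category to the pooling step: "sitting/rest (1 MET) and must be allocated to the right category. The number of minutes per category is then combined". The grade is "organized as high, moderate, or low physical activity based on the total MET minutes".

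So four categories are named, each has a MET weight, and the categories are pooled into the quantity that sets the grade. The section does not keep sitting out of that total, does not report it as a separate variable, and gives no cut-points for the three grades.

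The outcome appears in *Secondary outcome measures*, where the list of eleven ends with "10) level of physical activity and 11) sleep quality".

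**The concern.** A total meant to rank people by how active they are should not increase with time spent sitting. A weight of 1 looks small next to 3.3, 4 or 8, but people sit for hours a day and exercise for minutes, so the sitting term can be the largest in the sum.

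Two things are at stake. First, the ordering of participants, and hence the grade, may reflect sitting time more than activity. Second, change from baseline becomes hard to read. Someone who sits less and stands more loses points, and someone who turns sitting into walking gets only part of the credit.

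**Working it through.** **Inputs from the protocol article (IPAQ section).** Weights: vigorous 8, moderate 4, walking 3.3, sitting/rest 1. Window: 7 days. The section contains no worked total to reproduce.

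**Assumptions, not in the protocol.** Sitting 4 to 10 h/day. An illustrative active week of 150 min walking and 60 min moderate activity, with no vigorous activity.

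**Formula as written.** Total = 8 × vigorous + 4 × moderate + 3.3 × walking + 1 × sitting, all in minutes per week. The alternative omits the last term.

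**Step 1. Activity alone.** 3.3 × 150 + 4 × 60 = 495 + 240 = 735 MET-min.

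**Step 2. Add sitting.** Each hour per day contributes 60 × 7 × 1 = 420 MET-min per week.

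| Sitting (h/day) | Sitting MET-min | Total as written | Sitting share | Total without sitting |
|---|---|---|---|---|
| 4 | 1,680 | 2,415 | 70% | 735 |
| 6 | 2,520 | 3,255 | 77% | 735 |
| 8 | 3,360 | 4,095 | 82% | 735 |
| 10 | 4,200 | 4,935 | 85% | 735 |

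**Step 3. What one extra sitting hour per day is worth.** 420 MET-min equals 420/3.3 = 127 min of walking, 420/4 = 105 min of moderate activity, or 420/8 = 52.5 min of vigorous activity per week.

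**Step 4. Can the ranking reverse?**
- Person A: the active week above, sitting 6 h/day: 735 + 2,520 = 3,255.
- Person B: no activity, sitting 9 h/day: 0 + 9 × 420 = 3,780.
- As written, B ranks above A. Without sitting, A has 735 and B has 0.
- The break-even is 735/420 = 1.75 h/day. An inactive person who sits more than 1.75 h/day longer than A outranks A.

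**Step 5. The limit.** Replacing active minutes one for one with sitting lowers the total. For 60 min of walking the change is 60 × (1 − 3.3) = −138, and for 60 min of moderate activity it is 60 × (1 − 4) = −180. The total rises with sitting only when sitting takes the place of time that no category counts, or when added sitting outweighs lost activity.

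**Step 6. Effect on change scores.** A participant who turns 60 min of sitting into walking gains 198 MET-min when sitting is left out (60 × 3.3), but 138 as written (198 − 60). A participant who replaces one hour of sitting per day with uncounted time loses 420 with no change in activity.

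**The case against.** The strongest reply is that this section is a brief description of a published, cited questionnaire and not a scoring algorithm. It gives no explicit formula, and the team may intend to handle sitting separately. That is possible, and the document cannot settle it. But the article chose to state a rule. That rule gives sitting a weight and pools the categories with no exception. A stated rule that gives a wrong result is different from a detail left to a fuller document.

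Three further points stand as limits. The sitting hours are assumed. Without cut-points, no number of misclassified participants can be derived. And the outcome carries little weight in the trial: physical activity is absent from the stated purpose, the hypotheses and the sample size, and *Statistical analysis* names no between-group test for it. It is covered only by the descriptive summary of all primary and secondary outcomes and by the abstract's general statement about changes in all outcomes.

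A reader might also infer that the week-10 questionnaire counts the supervised sessions, so that a rise from baseline is built in and the arms are not comparable. The documents do not support this:
- Assessments "will be repeated at the end of the intervention during a 10-week follow-up", but the gap between the last session and the questionnaire is not given, and the appendix schedule table is not shown. If no session falls within the 7 days, the contribution is zero.
- Session frequency is the same in both arms: "The intervention period will last 10 weeks, with a frequency of 2 times a week for each group". Standard-care session length is not stated, so no difference between arms can be calculated.
- The outcome is named as level of physical activity, not as activity outside the trial. Whether respondents leave out sessions is an instruction on the form, which an article commonly leaves to other documents.

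**Conclusion.** The scoring rule is wrong as written: sitting enters the total that grades physical activity. Under the assumed 4 to 10 h/day it contributes 1,680 to 4,200 MET-min per week, can dominate the sum, and can rank an inactive person above an active one.

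It would be too strong to say that the score simply rises with inactivity, because minute-for-minute replacement of activity by sitting lowers it. Nor is a biased comparison between arms shown. Randomisation balances baseline sitting in expectation, so the contrast in means shifts only if the treatments change sitting differently. Otherwise the effect is added variation and a score whose direction is hard to interpret.

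The problem is confined to one of eleven secondary outcomes. It does not touch the multifidus primary outcome or the sample size. It is a minor point that is worth correcting because the correction is so cheap.

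**What to change.** Replace the pooling sentence in the IPAQ section with a rule that computes total MET-minutes per week, and the high, moderate or low grade, from walking, moderate and vigorous minutes only. Report sitting time as a separate variable in minutes. If the team already scores it this way, the same sentence makes that explicit.

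The cost is one scoring sentence. No new data are needed, because minutes are already collected by category, and the questionnaire and visit schedule do not change.

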#### Exploratory outcomes

1) feasibility of using the application in both groups, 2) adherence of using the application, and 3) participants’ satisfaction with the application.

##### Digital app “play the pain”

Participants in both groups will also be asked to use the digital application “play the pain”. To avoid an inadvertent co-intervention, the “Play’’ function of the app will not be used in the trial. The function of interest for this study is the “track’’ function. Participants will be able to track their pain, their activities, their sleep, their medication use and their emotions. The pain tracking function allows users to describe the location of the pain with an interactive model of the human body. After determining the location of the pain, users are prompted to scale the intensity with a movable cursor from slight pain to extreme pain. The emotion tracking features an interactive web with a wide range of feelings including: anxious, afraid, worried, happy, calm, etc. Each emotion can be clicked on and given an intensity ranging from “a little” to “a lot”. The sleep tracking function tracks the duration of sleep with a dichotomous scale. The two options are “more than 7 h’’ and “less than 7 h’’. After choosing an option, users are asked to describe the quality with a 5-point Likert scale. The options are: “Great”, “Good”, “OK”, “Not good” and “Very bad”. Each option is accompanied with a smiley face visually representing the choice. The medication tracking feature asks if the medication taken is prescribed or not, with an empty box for a description of the type of medication and the dosage. The activity tracking feature has 24 options to choose from. This feature includes physical activity including: exercise, dancing, walking, yoga, swimming, jogging and cycling. Additionally, included are treatment alternatives often used for chronic pain, such as, physiotherapy, cognitive behavioral therapy, meditation, acupuncture and recreational drug use. The last category of the activity tracking feature is focused on hobbies including: gaming, reading, painting and watching television. In addition, there is an “Other” section in order for other activities that were not included in the list to be described. Participants in the study will be asked to use the app on a daily basis. There are no specific guidelines on what should be tracked each day. The philosophy of Play the Pain is to let the user share what is on their mind, and to give the clinician a better understanding of their condition and how patients cope with pain [73, 74]. Participants will be introduced to the application when they come to the School of Health for their first visit, and will be provided with clear instructions on how to install it and use it. Each participant’s account will be linked to an administrative account managed by the research team, allowing us to track each participant and their use of the application. At the end of the intervention, the participants will be asked to complete and exit survey regarding their satisfaction with the use of the application.

## Data monitoring

### Adverse events

Adverse events (e.g., short-term increase in LBP and muscle soreness) will be monitored by the ATs during and following the interventions by asking open ended questions.

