However, it is difficult for those with LBP to perform strengthening exercises without avoiding the weight load on their spine [28]. In addition, fear avoidance beliefs which refer to fear of physical movement and work activities that may elicit pain is very common in individuals with chronic LBP [11, 12]. One form of exercise that has been suggested as a promising and safer treatment alternative for individuals with LBP is aquatic exercise, with less risk of injury and difficulty performing exercises [14, 29–35]. Water immersion decreases axial loading of the spine and, through the effects of buoyancy, allows the execution of movements that are usually difficult to perform on land by reducing stress in joints [36, 37]. The unique properties of water, such as buoyancy, allow a water-based exercise program to be tailored to the needs of those suffering from LBP. Aquatic exercise may improve pain and disability [38], and maintain quality of life in individuals with chronic LBP [35], especially in individuals with low levels of physical fitness [39, 40]. Improvements in muscle strength [41] and cardiovascular fitness [31, 42] through continuous limb movements against water resistance have been reported as well. A recent systematic review and meta-analysis on the effect of aquatic therapy in LBP, showed that this may not only be an effective alternative to conventional LBP treatments, but also a safe and enjoyable substitute to improve physical function [38]. These findings suggest the potential benefits of aquatic exercise for individuals with chronic LBP.

Recent reviews concluded there is no clear particular form of exercise that is more effective than others [17–19]. Interestingly, when comparing aquatic therapy to land-based exercise in individuals with chronic LBP, some study results have showed no significant differences in decreased pain levels or improved functional ability between the two exercise types [31, 34]. However, one study showed better improvements in functional ability in the aquatic therapy group compared to the land-based exercise group [35]. Moreover, Psych et al. showed that aquatic therapy produced comparable back and gluteal muscle activation and intensity to land-based exercise [43]. Overall, there are some inconsistencies between studies comparing aquatic therapy to land-based exercise in individuals with chronic LBP.

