### Blinding

Since blinding of therapists and participants is generally not possible in exercise intervention trials [50], only the assessor will be blinded.

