### Swim ex water-based trunk stabilization group (Swim Ex)

Participants in this group will perform trunk stabilization, which will be based on a variety of aquatic exercises in different positions, intended to activate the multifidus and transverse abdominis in a co-contraction. Additionally, hip and gluteal specific exercises will be completed to promote strengthening of the gluteus maximus, gluteus medius, and gluteus minimus muscles. The aim of these exercises is to enhance the strength and dynamic stability of the spine and its surrounding musculature in a functional and yet non-weight-bearing way. Each exercise will be performed 10 times while sustaining the muscles co-contraction for 5–10 s and will be progressed gradually by adding low load to the muscles by means of external leverage at the limbs (discs, hand paddles), resistance material (kickboard, dumbbell floats), water current and/or leg length, and by gradually adding repetitions. Each training session (~ 60 min) will be privately supervised one-on-one by a certified Athletic Therapist (AT) and take place in the School of Health AT Clinic/Swim Ex pool. The level of difficulty will be increased using the Borg Rating of Perceived Exertion Scale (1–10 scale) (e.g. set level three = moderate or four = somewhat hard) and the Category Ratio scale (0–10 pain scale) [52]. This aquatic exercise program (refer to Table 1) was adapted from a recent study in adults with chronic LBP [43].

**Table 1 Tab1:** Aquatic exercise program group

	**Aquatic Exercises**	**Volume**	
**Warm-Up** (10 min)	**Water walking:** forwards, backwards, sideways—left and right. Progressively increase walking speed	3 min (30 s / direction)	
	**Small hops:** feet shoulder width apart, squat, then jump and bring feet close together and squat back down	1 min (30 s/ direction)	
	**Leg kicks:** kick front, kick out by side, kick back	1 min (30 s / leg)	
	**Marching:** raise knees, heel to buttocks—as tolerated	2 min (1 min each)	
	**Horizontal kicking:** on stomach, while holding onto edge of pool, kick legs and try to maintain body horizontal. Use floating device under the waist to modify difficutly	1 min (30 s each)	
	**Upper body oscillations:** Moving both arms in an oscillatory fashion from in front of you to out by your side	1 min	
	**Bow and Arrow:** rotate the torso by bringing your arms close to your body as if you’re shooting a bow and arrow. Alternate sides	1 min	

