### Standard care group

Participants in this group will receive the standard LBP treatment in the School of Health Athletic Therapy clinic and will be privately supervised one-on-one by a certified AT who will be conducting the sessions. The AT will complete a thorough assessment of the eligible participants with chronic LBP and administer a range of interventions including stretching, strengthening and stabilization exercise, aerobic conditioning, and manual mobilization techniques. No attempt will be made to try to regulate/standardize the treatment received, however information about pain medication and co-interventions will be collected throughout the duration of the study.

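### Adverse events are elicited only by open-ended questions from unblinded therapists, which leaves the counts open to observer bias and possibly to unequal ascertainment between arms

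*Protocol article*

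**What the plan says.** The Adverse events section of the protocol article is one sentence. It gives two examples, "Adverse events (e.g., short-term increase in LBP and muscle soreness", and says that events "will be monitored by the ATs during and following the interventions by asking open ended questions". No other means of finding adverse events is stated.

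The surrounding sections fix who asks and in what setting:

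- **Blinding:** therapists and participants are not blinded; "only the assessor will be blinded". Adverse events are assigned to the ATs, not to that assessor.
- **Aquatic arm (Swim Ex section):** each session "will be privately supervised one-on-one by a certified Athletic Therapist (AT". Difficulty is raised with the Borg exertion scale and "the Category Ratio scale (0–10 pain scale".
- **Standard care group:** participants "will be privately supervised one-on-one by a certified AT who will be conducting the sessions". No pain scale is named for these sessions, and "No attempt will be made to try to regulate/standardize the treatment received".
- **Abstract, Methods:** both arms have 20 supervised sessions over 10 weeks.
- **Background:** aquatic exercise is introduced, from earlier literature, as a "safer treatment alternative for individuals with LBP is aquatic exercise, with less risk of injury".

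**The concern.** Two features of the stated method matter.

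First, an open question has no fixed wording and no stated threshold. Every participant enters with LBP of more than three months and moderate or severe disability. Whether a given day's pain is a short-term increase or ordinary fluctuation is therefore left to the judgement of someone who knows the treatment and, in all likelihood, is delivering it.

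Second, the aquatic therapists have a named reason to ask for a pain number and the standard care therapists do not. A therapist who has just heard a number rise may be more likely to note an event.

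The two influences can act in opposite directions. The extra prompt could raise the aquatic count. A therapist's expectation that water is gentler could lower it. The reader of the results could not separate these from a real difference.

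At stake is the only safety information the article says will be collected. Readers of a two-arm trial tend to set event counts side by side even when no test is planned, and the abstract says the findings will feed into the design of a community program.

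**Working it through.** The article gives no adverse event figure to reproduce, so the check is mainly a reading of the sections against each other.

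**1. Is the stated method the same in both arms?** Yes. The Adverse events sentence covers both interventions, the questioners are ATs in both, supervision is one-on-one in both, and there are 20 sessions in each. Opportunity to detect is equal by design.

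**2. Is the questioner the treating therapist?** This is not stated outright. It follows by inference, because the ATs ask during as well as after the intervention and each session is one-on-one with an AT.

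**3. Does the pain scale create an asymmetry?** It is named only in the aquatic section, and its stated purpose is exercise progression. Its frequency, its recording and any link to adverse event reporting are not stated. The asymmetry is therefore possible, not established.

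**4. Does anything else in the article repair the weakness?**

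- The numerical pain rating is taken in both arms, but the Data collection section places it at baseline and at the 10-week follow-up. It cannot show a short-term rise between those points.
- The app is offered to both arms for daily use and can hold pain intensity. What is tracked each day is left to the participant, and app entries are not linked to adverse events.

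**5. How large could the effect be?** Only an illustration is possible. Let p be the true risk per participant, equal in both arms, and let s be the probability that an event is detected and recorded.

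Expected recorded count per arm = 17 × p × s, so the ratio of counts (aquatic / standard) = s_aquatic / s_standard. The value of p cancels.

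With n = 17 per arm (Sample size justification) and p = 0.40 assumed:

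| Assumed s, aquatic / standard | Expected counts | Ratio |
|---|---|---|
| 0.7 / 0.7 | 4.76 vs 4.76 | 1.00 |
| 0.8 / 0.6 | 5.44 vs 4.08 | 1.33 |
| 0.9 / 0.5 | 6.12 vs 3.40 | 1.80 |

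If therapist expectation dominated and the detection values were reversed, 0.6 / 0.8 would give 0.75.

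Per session, 17 × 20 = 340 planned sessions per arm. At an assumed 15% flare rate there are 0.15 × 340 = 51 true flares in each arm. Detection of 0.9 and 0.5 gives 45.9 and 25.5 recorded, again a ratio of 1.80. A milder 0.80 / 0.65 gives 1.23.

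These ratios only restate the assumed detection probabilities. They show how sensitive a comparison would be. They do not estimate bias in this trial.

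**The case against.** The strongest reply is that the trial plans no comparison of adverse event counts. They appear under Data monitoring only. They are not a primary, secondary or exploratory outcome, no hypothesis concerns safety, and the Statistical analysis section does not mention them. The description of aquatic exercise as safer is background from earlier literature, not something this trial sets out to test. All of this stands, and it limits the weight of the point.

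A reader might infer that the aquatic arm has a pain score at every session and that adverse event counts therefore cannot be compared at all. The article does not support this. It does not say the scale is used at each session, that scores are kept, or that they reach the adverse event record. The stated method, the type of questioner and the number of sessions are the same in both arms. The sentence declining to standardize concerns the treatment received, not the monitoring. The standard care AT also carries out a thorough assessment, so it cannot be assumed that no pain rating is ever asked there.

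It can also be said that unblinded therapists are unavoidable here, which the article acknowledges, and that question wording and thresholds are often left to the full protocol. Both are fair. The point does not rest on missing detail, however. It rests on the method that is stated, open-ended questions from unblinded ATs, and a better one is available at little cost without blinding anyone.

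**Conclusion.** The point holds in a limited form. As stated, adverse events are found solely by unstructured questions from unblinded ATs, in people whose existing pain makes one of the example events hard to judge. Counts are therefore open to observer bias. They may also be ascertained unequally, because a 0-10 pain scale is named in one arm only.

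The documents do not show that unequal ascertainment occurs or how large it would be. The illustrative ratios of 1.00 to 1.80 depend wholly on assumed detection probabilities and on equal true risk. The conclusion also rests on the inference that the questioner is the treating therapist; if it were another unblinded AT, the concern would be weaker but would remain. Since no between-arm analysis of adverse events is planned, no stated analysis is invalidated. This is a worthwhile, low-cost improvement to the trial's safety data.

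**What to change.** In the Adverse events section, keep the open question and add the same brief record at every session in both arms:

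- a 0-10 LBP rating before and after the session;
- one question with fixed wording on worsening of LBP or soreness since the last session;
- a change in the rating, specified in advance, that counts as a recorded increase in LBP.

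This definition is for recording only and need not alter treatment in either arm. Report events per session attended, by arm, descriptively. Draw no comparative safety conclusion from the open-ended reports alone.

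The cost is about one minute per session, and the record can go in the treatment file the ATs already use for adherence. Recorded event counts will rise, which the report should explain. The added record makes the wording and threshold the same in both arms. It does not remove bias from unblinded participants or therapists.
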